## Abstract

**Background::**

Community-acquired pneumonia (CAP) is a major global disease. Parapneumonic effusions often complicate CAP and range from uninfected (simple) to infected (complicated) parapneumonic effusions and empyema (pus). CAP patients who have a pleural effusion at presentation are more likely to require hospitalization, have a longer length of stay and higher mortality than those without an effusion. Conventional management of pleural infection, with antibiotics and chest tube drainage, fails in about 30% of cases. Several randomized controlled trials (RCT) have evaluated the use of corticosteroids in CAP and demonstrated some potential benefits. Importantly, steroid use in pneumonia has an acceptable safety profile with no adverse impact on mortality. A RCT focused on pediatric patients with pneumonia and a parapneumonic effusion demonstrated shorter time to recovery. The effects of corticosteroid use on clinical outcomes in adults with parapneumonic effusions have not been tested. We hypothesize that parapneumonic effusions develop from an exaggerated pleural inflammatory response. Treatment with systemic steroids may dampen the inflammation and lead to improved clinical outcomes. The steroid therapy and outcome of parapneumonic pleural effusions (STOPPE) trial will assess the efficacy and safety of systemic corticosteroid as an adjunct therapy in adult patients with CAP and pleural effusions.

**Methods::**

STOPPE is a pilot multicenter, double-blinded, placebo-controlled RCT that will randomize 80 patients with parapneumonic effusions (2:1) to intravenous dexamethasone or placebo, administered twice daily for 48 hours. This exploratory study will capture a wide range of clinically relevant endpoints which have been used in clinical trials of pneumonia and/or pleural infection; including, but not limited to: time to clinical stability, inflammatory markers, quality of life, length of hospital stay, proportion of patients requiring escalation of care (thoracostomy or thoracoscopy), and mortality. Safety will be assessed by monitoring for the incidence of adverse events during the study.

**Discussion::**

STOPPE is the first trial to assess the efficacy and safety profile of systemic corticosteroids in adults with CAP and pleural effusions. This will inform future studies on feasibility and appropriate trial endpoints.

**Trial registration::**

ACTRN12618000947202

**Protocol version::**

version 3.00/26.07.18

## Introduction

1

Community-acquired pneumonia (CAP) is a major global disease.^[1]^ Pneumonia (including influenza) is currently the 8th leading cause of death in the United States^[2]^ and lower respiratory tract infections were the 3rd leading cause of death worldwide in 2015.^[3]^ CAP incurs significant, immediate, healthcare costs as well as economic costs of time lost from work/school and adverse long-term health problems in survivors.^[4,5]^

Parapneumonic effusions complicate 18% to 57% of cases of pneumonia.^[6–8]^ CAP with an effusion is associated with worse outcomes. In one large study of 4700 patients with CAP, those with an effusion at the time of presentation to the emergency department were more likely to require hospitalization and had a length of stay twice that of those without an effusion.^[9]^ Parapneumonic effusions, inadequately treated, may progress to complicated parapneumonic effusions or empyema, both of which have risen in incidence in recent years.^[10,11]^ Conventional management of pleural infection, with antibiotics and chest tube drainage, fails in about 30% of cases. Many of these patients are frail and unsuitable for surgical management and mortality remains high at 8% in hospital and 20% at 3 months.^[11]^ This mortality rate has increased over the past 2 decades, despite advances in antimicrobial therapy.^[12]^

The pathobiology of pleural effusion formation secondary to pneumonia is not fully understood. One hypothesis is that an over-exaggerated inflammatory response triggered by the infection plays a critical role and may be a target for treatment. Steroids have been shown to be successful adjunct therapies in pneumococcal meningitis and Pneumocystis jirovecii pneumonia, likely due to the significant inflammatory component of these conditions.^[13,14]^ The role of systemic corticosteroids as adjunct treatment in pneumonia is a controversial topic with inconsistent results on mortality from large randomized contolled trials (RCTs).^[15]^ The majority of studies have, however, demonstrated benefits of steroids in shortening time to resolution of fever and clinical stability.^[16–22]^ Importantly, all the studies have demonstrated that use of steroids, even in severe pneumonia, was safe with no adverse impact on mortality.^[23,24]^

The effects of corticosteroid use on clinical outcomes in adults with parapneumonic effusions have not been tested, however, evidence exists in support of the hypothesis that parapneumonic effusions develop from an exaggerated immune response. Patients on long-term inhaled corticosteroids were much less likely to develop a parapneumonic effusion compared with those who were not, and in those who developed a parapneumonic effusion, it was significantly smaller in volume with lower inflammatory indices.^[25]^ Similarly, addition of prednisolone offered faster symptomatic improvement over placebo without major side effects in tuberculosis pleural effusions.^[26]^ Only one study has directly assessed the impact of steroids in parapneumonic effusion. This RCT of pediatric patients found that children treated with dexamethasone infusion had a shorter time to recovery without detrimental impact, except for transient hyperglycemia.^[27]^ These findings strongly support evaluation of the role of adjunct corticosteroid therapy in adults with pneumonia and associated pleural effusions.

The steroid therapy and outcome of parapneumonic pleural effusions (STOPPE) trial is a pilot multicenter, double-blinded, placebo-controlled RCT designed to assess the efficacy and safety of systemic corticosteroid as an adjunct therapy in patients with parapneumonic pleural effusions. The primary hypothesis is that systemic corticosteroids will improve clinical outcome (by reducing pleural and systemic inflammation) in patients with pneumonia-related pleural effusions, and have an acceptable safety profile.

## Methods

2

### Study design and participants

2.1

STOPPE is a multicenter, double-blinded, placebo-controlled RCT which will recruit participants with parapneumonic effusion. Participants will be randomized 2:1 to receive intravenous dexamethasone (4 mg twice daily for 48 hours) or placebo. This study will follow participants through their hospital admission and at outpatient visits after 14 days, 30 days, 6 months, and 12 months (Table 1).

**Table 1 T1:**
[figure not shown]
Schedule of enrolment, intervention, data collection, and assessment.

Patients with community-acquired pneumonia will be identified on hospital admission to the General Medicine and Respiratory teams. Those who have a pleural effusion either on admission or develop one within the following 72 hours will be identified. Any patient that meets the inclusion criteria, and none of the exclusion criteria, will be approached by a member of the research team and offered inclusion in the trial. Informed consent will be obtained prior to enrolment. Screening logs will be kept.

Inclusion criteria: New pleural effusion on chest radiography (with bedside ultrasound confirmation) with clinical evidence of a community-acquired pneumonia as per clinician assessment and no alternative causes identified.

Exclusion criteria (similar to those used in recent large multicenter trials of corticosteroid use in pneumonia):

1.Age <18 years;2.Hemodynamic/respiratory instability requiring intensive care;3.Acute burn injury;4.Gastrointestinal bleeding in the last 3 months;5.Known adrenal insufficiency;6.Other indication for steroids (e.g., asthma/COPD exacerbation);7.Long-term steroid use (≥10 mg/d prednisolone equivalent);8.Acute delirium;9.Previous steroid-induced psychosis;10.Severe immunodeficiency (e.g., HIV infection and CD4 count <350 cells/μL), immunosuppressive therapy after organ transplant, leukocytopenia (<1 × 10^9^/L);11.Cystic fibrosis;12.Active tuberculosis;13.Pregnancy/lactation;14.Un-correctable bleeding diathesis;15.Poorly-controlled diabetes mellitus (DM);16.Blood glucose level over 20 mmol/L at the time of screening; and17.Inability to consent.

### Interventions

2.2

This trial will randomize participants to receive either dexamethasone 4 mg or placebo administered as an intravenous infusion every 12 hours for 48 hours, that is, to a total of 4 doses. Dexamethasone will be diluted in 100 mL of normal saline and administered via a standard intravenous administration line as a 15-minute infusion. The placebo arm will receive 100 mL of normal saline similarly administered via standard intravenous administration line. Once randomized, the hospital pharmacy will prepare the assigned drug (or placebo). Participants, clinicians, nursing staff, and the research team will be blinded to the treatment arm.

Participants may be withdrawn from the trial if they develop a severe adverse event (SAE). After the identification of a SAE during administration of study drug, dexamethasone/placebo administration may be interrupted for up to 24 hours at the discretion of the local principal investigator and restarted if clinically appropriate to complete the delayed trial treatment course. Participants may also withdraw from the trial at any time if they so wish.

Participants will be able to take their usual medications during the study. Any changes required will be discussed with the participant prior to recruitment. A note of all medications will be taken before the start of the study and will be entered on to the participant's medication log.

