### Sample size

2.4

In the absence of existing data, this pilot study aims to recruit 80 participants over 18 months. This will allow inclusion of the full range of parapneumonic effusions at various stages from simple parapneumonic stage (most common) to empyema (about 5–10% of all cases). The 2:1 randomization strategy will include 50+ participants into the dexamethasone arm to increase the power of detecting treatment related adverse events. The results of this pilot study will inform the power calculation of future studies and determine the most appropriate endpoints of future trials. Past evidence and data suggest that we will be able to estimate a range of outcome parameters with a high enough degree of accuracy with a sample size of 80 and allow some initial comparisons between treatment and placebo. The number of patients included over this timeframe will inform the feasibility and design of further studies.

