### Statistical methods

2.8

Data will be analyzed on an intention-to-treat basis. Intergroup comparison will be conducted using Student *t* test or Mann–Whitney *U* rank sum test (for parametric and non-parametric distributions, respectively). Changes in parameters before and after treatment within the same subject will be analyzed using a paired *t* test or Wilcoxon signed rank test. Correlations will be analyzed using Pearson or Spearman tests. Multivariate analyses may be performed if indicated. *P* < .05 will be considered statistically significant in the data analyses.

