### Data monitoring

2.9

The Trial Steering Committee will be responsible for the supervision of the trial in all its aspects. It will be responsible for ensuring the completion of the trial to clinical and ethical standards. The Data Safety Monitoring Committee will ensure the safety of study participants through study procedures, reviewing adverse events and serious adverse events, and consider new data (recently published studies) that may determine the validity of study continuation. All deaths, anticipated or unanticipated, will be discussed with the Data Safety Monitoring Committee (DSMC). The committee determines whether significant benefits or risks have been uncovered which may have an impact on the feasibility and/or ethical conduct of the study. The DSMC will also help to ensure the scientific integrity of the study by reviewing the quality of the data it uses to make its decisions.

All serious and non-serious adverse events (AEs) relating to the study will be fully documented on the appropriate case report forms (CRFs). For each AE, the investigator will provide the onset and end dates, intensity, treatment required, outcome, seriousness and action taken. AE logs will be followed up until resolution. Where AEs are not resolved at study completion this will be noted on the AE log.

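### An SAE can end trial participation, not just study drug, and nothing keeps these participants in follow-up, so later outcomes can be lost in an outcome-dependent way

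*Protocol article*

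**What the plan says.** Section 2.2 (Interventions) of the protocol article has three separate provisions:

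- Leaving the trial because of an event: "Participants may be withdrawn from the trial if they develop a severe adverse event (SAE".
- Handling of study drug after an SAE: "dexamethasone/placebo administration may be interrupted for up to 24 hours at the discretion of the local principal investigator", with restart possible.
- The participant's own choice: "Participants may also withdraw from the trial at any time if they so wish".

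Section 2.8 (Statistical methods) states: "Data will be analyzed on an intention-to-treat basis". Section 2.1 sets the observation period: "This study will follow participants through their hospital admission and at outpatient visits after 14 days, 30 days, 6 months, and 12 months". Section 2.3 lists any-cause readmission among the adverse events (outcome 11) and overall survival as outcome 12. Section 2.4 ties the allocation ratio to safety: "The 2:1 randomization strategy will include 50+ participants into the dexamethasone arm to increase the power of detecting treatment related adverse events".

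Section 2.9 (Data monitoring) states: "All serious and non-serious adverse events (AEs) relating to the study will be fully documented". It adds that adverse-event logs are followed to resolution and that every death is discussed with the Data Safety Monitoring Committee (DSMC).

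**The concern.** An SAE is itself an outcome in a trial whose hypothesis includes acceptable safety. Several events in outcome 11, such as intensive care, nosocomial infection or gastrointestinal bleeding, could be the SAE that leads to withdrawal. Reaching one safety endpoint may then end observation of the others. Participants who have had an SAE are also likely to be at higher risk of later readmission and death, so their missing data would be informative.

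Two uses of the data are at stake. One is the comparison of the arms on later outcomes, which is distorted if the arms lose different proportions of high-risk participants. The other is the pilot's purpose of informing the power calculation for later trials, which suffers even under equal loss because event rates would be too low. No later analysis can recover follow-up that was never collected.

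**Working it through.** **1. What the rule means.** Interruption of drug and voluntary withdrawal each have their own sentence in section 2.2, so the SAE sentence is not simply another way of saying either. The missed-visit procedure in section 2.6 covers non-attendance and admission to hospital, not withdrawal. Section 2.9 keeps the triggering event on record. What remains unprotected is everything after it: later events, readmission, late survival and the scheduled measures from day 14 to month 12.

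**2. The plan's own figure.** Section 2.4: "this pilot study aims to recruit 80 participants over 18 months", allocated 2:1. Dexamethasone: 80 × 2/3 = 53.3. Placebo: 80 × 1/3 = 26.7. Using 53 and 27, the stated 50+ on dexamethasone is reproduced.

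**3. How many could lose later follow-up.** The article gives neither an SAE rate nor the share withdrawn, so both are assumed. Loss per arm = arm size × SAE rate × share withdrawn.

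| SAE rate, dexamethasone / placebo | Share withdrawn | Lost, dexamethasone | Lost, placebo | Total of 80 |
|---|---|---|---|---|
| 5% / 5% | 50% | 1.3 | 0.7 | 2.0 (2.5%) |
| 10% / 10% | 50% | 2.7 | 1.4 | 4.0 (5%) |
| 10% / 10% | 100% | 5.3 | 2.7 | 8.0 (10%) |
| 20% / 10% | 100% | 10.6 | 2.7 | 13.3 (16.6%) |
| 20% / 20% | 100% | 10.6 | 5.4 | 16.0 (20%) |

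The dexamethasone arm under full follow-up falls from 53 to between about 52 and 42 (53 − 10.6 = 42.4).

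**4. Numbers alone.** For a late adverse event with a true rate of 3%, the chance of seeing at least one is 1 − 0.97^53 = 80% with 53 participants and 1 − 0.97^42 = 72% with 42. The drop is modest. The selection of who is lost matters more.

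**5. Effect on mortality.** Assume later mortality of 40% after an SAE and 10% otherwise. With SAE risk s and share withdrawn w:

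- true mortality = 0.40s + 0.10(1 − s)
- mortality among those retained = [0.40s(1 − w) + 0.10(1 − s)] / (1 − sw)

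*SAE risk 20% on dexamethasone, 10% on placebo.*

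- True: 0.08 + 0.08 = 16.0% v 0.04 + 0.09 = 13.0%, a difference of 3.0 points.
- Half withdrawn: (0.04 + 0.08)/0.90 = 13.3% v (0.02 + 0.09)/0.95 = 11.6%, a difference of 1.8 points from unrounded rates.
- All withdrawn: 0.08/0.80 = 10.0% v 0.09/0.90 = 10.0%, no difference.

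*Rates reversed (10% on dexamethasone, 20% on placebo).* The same figures apply with the arms exchanged, so a true benefit of dexamethasone shrinks in the same way.

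*Equal SAE risk of 10%, equal withdrawal.* True mortality is 13.0% in both arms. Observed mortality is 11.6% (half withdrawn) or 10.0% (all withdrawn) in both. The difference stays at zero, but the rate is understated.

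*Equal SAE risk of 10%, unequal withdrawal (half in one arm, all in the other).* Observed 11.6% v 10.0%, a spurious difference of about 1.6 points.

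**The case against.** The strongest reply is that the rule is permissive and sits in a section about dosing, beside a provision for interruption and restart that presumes some participants with an SAE carry on. Section 2.6 shows an intent to retain sick patients: non-attenders are contacted, and visits missed through admission are done in hospital where possible. This is an exploratory pilot with four doses over 48 hours, and several outcomes are early and in hospital. Follow-up after withdrawal may be settled in the full protocol or the analysis plan, neither of which is shown. Blinding also makes it less likely that withdrawal after an SAE depends on the arm.

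Much of this stands as a limit on size. It does not change what the article states, which is exit from the trial because of an event, with no words that keep the participant under observation. Blinding does not equalize the SAE rates themselves.

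A reader might also infer more than the text supports:

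- *That the SAE itself drops out of the safety data.* It does not; section 2.9 has adverse events documented and followed to resolution. Deaths go to the DSMC, although a death after withdrawal can be discussed only if the trial learns of it.
- *That intention to treat is defeated.* Withdrawn participants can still be analysed as randomized on data up to withdrawal.
- *That the bias favours dexamethasone.* This holds only if dexamethasone has more SAEs or more withdrawals. The trial's own hypothesis is compatible with fewer.
- *That a causality judgement filters adverse events before the arms are compared.* That is one reading of "All serious and non-serious adverse events (AEs) relating to the study will be fully documented". The abstract (incidence during the study), any-cause readmission in section 2.3, and the monitoring of all participants in section 2.6 favour the unfiltered reading.

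**Conclusion.** The point holds in a limited form. Followed as written, section 2.2 allows outcome-dependent loss of later data. This is at odds with the intention-to-treat statement in section 2.8, the 12-month follow-up in section 2.1, and the readmission and survival outcomes in section 2.3. It weakens the safety aim but does not erase the triggering events.

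The size cannot be fixed from the article. The range of 2 to 16 of 80 rests wholly on the assumed SAE rates and shares withdrawn. The mortality figures rest on further assumptions: the 40% and 10% risks, and that deaths after withdrawal go unobserved. Complete disappearance of a difference is the extreme case, in which every participant with an SAE leaves; with half leaving, 1.8 of 3.0 points remain. The finding that equal rates leave the difference undisturbed belongs to the illustration, where risk after an SAE is the same in both arms.

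The use of *severe* in section 2.2 and *serious* in section 2.9 for what appears to be the same category is an editorial matter. It leaves the trigger for withdrawal unclear but adds no weight to the main point.

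**What to change.** Reconcile sections 2.2, 2.8 and 2.9:

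1. Separate any decision about study drug from withdrawal from follow-up.
2. State that all randomized participants, including those with an SAE, stay in the planned follow-up and analysis to 12 months unless they withdraw consent to data collection.

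When study drug is stopped, interrupted or restarted is a clinical matter, and no rule for it is proposed here.

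Two secondary clarifications can go in the same amendment: state in section 2.9 that adverse events are recorded irrespective of relatedness, and reconcile *severe* with *serious*.

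The cost is a short protocol amendment with ethics approval. It needs no visits beyond those already scheduled and at most a little more adverse-event recording. It helps only participants whose follow-up has not yet been ended, so it is best made early.

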### Outcomes

2.3

As a pilot and first study of corticosteroid in adults with pneumonia-related pleural effusions, we aim to capture a wide range of clinically relevant endpoints which have been used in clinical trials of pneumonia and/or pleural infection, and are considered by clinicians as important. These include:

1.The time to clinical stability defined as the time in hours for all of the following parameters to have been maintained for at least 12 hours: temperature ≤37.4°, heart rate ≤100 bpm, respiratory rate ≤20/min, oxygen saturations ≥95% on room air (unless on home oxygen), systolic blood pressure ≥90 mmHg and tolerating oral intake or discharge home (determined by the treating physician)^[28]^;2.The time in hours for each of the above parameters to have been maintained for least 12 hours;3.Change in leukocyte count and C-reactive protein (CRP) over time (Day 0, 1, 3, 14 ± 2 days, 30 ± 2 days);4.Proportion of participants with a normal leukocyte count and CRP at Day 14 ± 2 and Day 30 ± 2;5.Improvement in pleural effusion including size of pleural opacity as percentage of hemithorax (as used in our prior studies)^[29]^ over the first 14 ± 2 days and at Day 30 ± 2 compared with baseline; and proportion of participants whose effusion has resolved at day 14 ± 2 days and day 30 ± 2;6.Proportion of participants requiring an invasive pleural procedure including therapeutic aspirate (volume >200 mL) or chest drain insertion at <48 hours and >48 hours post-commencement of treatment. If intercostal catheter is inserted, the following will be recorded:a.Duration of chest tube drainage;b.Volume of fluid drained daily;c.Proportion treated with intrapleural fibrinolytic therapy; andd.Proportion requiring additional drainage procedures including additional chest drain insertion and therapeutic thoracentesis.7.Proportion of patients referred for thoracic surgery;8.Duration of antibiotic therapy (intravenous and oral);9.Length of hospital stay from commencement of treatment to discharge or death;10.Quality of life measurements including Short form-36 (SF-36) questionnaire^[30]^ and actigraphy (see Section 2.7 for details);11.Adverse events including but not limited to hyperglycemia, insulin use, need for intensive care, nosocomial infection, gastrointestinal bleeding and re-admission to hospital of any cause; and12.Overall survival.

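### Time to clinical stability can be scored wholly within the 48-hour dosing course, and no listed outcome records stability lost afterwards

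*Protocol article*

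**What the plan says.** Section 2.3 (Outcomes) lists twelve outcomes and names none as primary. Item 1 is "The time to clinical stability defined as the time in hours for all of the following parameters to have been maintained for at least 12" hours. The first three criteria are to be "maintained for at least 12 hours: temperature ≤37.4°, heart rate ≤100 bpm, respiratory rate ≤20/min", and the rest are "oxygen saturations ≥95% on room air (unless on home oxygen), systolic blood pressure ≥90 mmHg and tolerating oral intake or discharge home". All must hold together. Item 2 applies the same hold to each criterion on its own: "The time in hours for each of the above parameters to have been maintained for least 12 hours".

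Section 2.2 (Interventions) has dexamethasone or placebo "administered as an intravenous infusion every 12 hours for 48 hours, that is, to a total of 4 doses". Section 2.3 does not tie the 12-hour window to the end of dosing, asks for no persistence after the hold, and does not say what happens if a criterion is lost again.

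The hypothesis in section 1 is that "systemic corticosteroids will improve clinical outcome (by reducing pleural and systemic inflammation") and that safety is acceptable. The same section reports that most steroid trials in pneumonia shortened the time to fever resolution and to clinical stability. Section 3 describes dexamethasone as mainly anti-inflammatory. Section 2.4 gives the pilot the task of informing power and endpoint choice for later trials, and section 2.8 treats P < .05 as significant.

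**The concern.** The drug under test is expected to act directly on at least one scored criterion, temperature, while it is being given. A participant whose fever is held down for 12 hours during the course, and returns afterwards, can keep an early time to stability. Randomization and blinding do not remove this, because it is an effect of the drug on the measurement itself.

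The hypothesis concerns clinical outcome. As defined, the endpoint cannot separate an effect limited to the dosing period from one that lasts. If the difference between arms were of the first kind, the pilot could still recommend time to stability as an endpoint and supply its effect size for the next power calculation.

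**Working it through.** **1. The plan's own figures.** Doses: 48 / 12 = 4, nominally at 0, 12, 24 and 36 h, as stated. Arms: 80 × 2/3 = 53.3 and 80 × 1/3 = 26.7, so about 53 v 27, in line with the stated 50+ on dexamethasone. No power, effect size or SD is given, so there is no power figure to reproduce.

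**2. Does the window fit inside the course?** A window starting at s ends at s + 12. It lies inside the course if s + 12 ≤ 48, that is, 0 ≤ s ≤ 36. Stability can therefore be scored from 12 h to 48 h while the course runs. The hold is 12 / 48 = 25% of the course.

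**3. When does masked fever bring the time forward?** Let F be the time at which fever truly resolves and O the time at which all other criteria are met.
- Item 1, fever not masked: T = max(F, O) + 12.
- Item 1, fever fully masked from 0 to 48 h: T = O + 12 if O + 12 ≤ 48 or F ≤ 48; otherwise max(F, O) + 12. The most that can be gained is max(F, O) − O, which is zero whenever O ≥ F.
- Item 2, temperature alone: F + 12 becomes 12 h under full masking, whatever the other criteria do.

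**4. How large could it be for item 1?** Every clinical input here is assumed; none is in the document. F and O are independent and lognormal with log-SD 0.7. Fever is fully masked on dexamethasone from 0 to 48 h only, the other criteria are unaffected by drug, and there is no true benefit. Arms are 53 v 27, compared by two-sided Mann–Whitney at 0.05, with 1,500 trials per row. Durable means that a masked participant with F > 48 loses stability at 48 h and is re-timed at max(F, O) + 12.

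| Median F / O (h) | P < .05, as written | Difference in medians (h) | Dexamethasone participants scored stable with fever truly lasting past 48 h | P < .05, durable | P < .05, no masking |
|---|---|---|---|---|---|
| 48 / 24 | 99.8% | −31 | 36% | 9.5% | 4.9% |
| 72 / 36 | 90.7% | −42 | 36% | 4.1% | 4.4% |
| 24 / 24 | 66.5% | −11 | 12% | 20.7% | 4.5% |
| 36 / 36 | 50.0% | −16 | 17% | 6.1% | 5.3% |
| 24 / 48 | 9.3% | −4 | 5% | 5.9% | 5.5% |
| 36 / 72 | 5.7% | −3 | 5% | 4.3% | 4.6% |
| 12 / 60 | 4.9% | −0.8 | 0.6% | 4.7% | 4.7% |

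The result turns on which criterion is slowest. The durable version removes most of the excess but not all of it: fever that is masked and then truly resolves before 48 h leaves no visible loss of stability, which is why 24 / 24 stays at 20.7%.

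**5. A cruder check without a mechanism.** Assume identical durable times in both arms (median 72 h, log-SD 0.8). Give a fraction f of the dexamethasone participants still unstable at 48 h one qualifying time between 12 and 48 h. For f = 0, 10, 20, 30 and 40%, P < .05 occurs in about 5, 8, 17, 33 and 56% of 2,500 trials, and the dexamethasone median looks about 0, 8, 17, 24 and 30 h shorter. Transient windows are given to dexamethasone only, so the bias is an input; this shows sensitivity, not likelihood.

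**The case against.** Item 1 is a composite. Saturation on room air, systolic pressure and oral intake or discharge must hold over the same 12 hours, so suppressed fever alone does not score. This stands, and it limits the point for item 1. It does not help the temperature time in item 2.

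The definition cites a published source, and the article does not use the word first. How repeated windows and relapse are handled could sit in the full protocol or analysis plan. That is fair for the derivation detail. But the article itself fixes the criteria, the hold and the list of outcomes, and a time until criteria have been held for 12 hours reads most naturally as the first such window.

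Other outcomes look past dosing: procedures after 48 h, surgical referral, antibiotic duration, length of stay, readmission, and effusion and inflammatory markers at Days 14 and 30. Day 3 CRP also falls after the last nominal dose at 36 h. A purely transient effect should leave these unchanged, which is a real safeguard on interpretation. None of them records a criterion lost in hospital after dosing, however, and no CRP or leukocyte measurement is listed between Day 3 and Day 14.

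A reader might go further and infer that antipyresis counts as recovery, that the trial's leading endpoint is invalid, or that a placebo participant can become stable only through the course of the illness. The documents support none of these. The event is called clinical stability, no outcome is primary, antibiotics and drainage appear as outcomes for all participants, and ordinary fluctuation can give a placebo participant a passing 12-hour window.

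**Conclusion.** The point holds in a limited form. A qualifying window can lie wholly within the dosing course, and nothing listed records stability lost afterwards. For the temperature time in item 2, suppression during dosing is itself the scored event. For item 1 it matters only where temperature, or a rate that follows it, is the last criterion outstanding.

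The size cannot be determined from the document. The range from 5% to 99.8% rests on assumed medians, assumed complete masking to 48 h, no drug effect on the other criteria and no transient windows on placebo. A reader might take the upper figures as the trial's false-positive rate; they only show that the answer depends on something the protocol does not report. Nor is faster resolution of fever necessarily spurious: the definition simply cannot tell a lasting effect from a passing one.

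The consequence is confined to items 1 and 2 and their use as candidate endpoints and sources of effect sizes for later trials. It does not undermine the pilot as a whole.

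**What to change.** - Keep items 1 and 2 as published, for comparability, and state that the first qualifying window is scored.
- Add a sensitivity analysis of durable stability: the first window meeting all criteria for at least 12 hours after which no criterion is lost through a prespecified horizon past the last study dose, or until discharge if earlier. A horizon of 24 h is an example and an assumed figure; on the nominal schedule it ends at 36 + 24 = 60 h. Keep the 12-hour hold for participants who stabilise later than that. Section 2.2 allows dosing to be interrupted for up to 24 h, so say how the horizon is counted in such cases.
- Report by arm the proportion who meet item 1 and then lose any criterion before discharge.
- Interpret an effect on time to stability alongside these two results. In an exploratory pilot they should inform the reading, not act as a gate.

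The cost is a little more derivation. Section 2.6 says clinical observations are repeated through the hospital stay, although the schedule table is not visible, so the low cost assumes they are frequent enough to show a lost criterion. Durable times will be somewhat longer, participants discharged early are classified at discharge, and masked fever that resolves within the course will still go undetected. Dosing, visits and sample size do not change.
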